#### Dehydration and Acute Renal Events

Renal safety will be assessed based on repeated renal functional assessment and assessment of AEs suggestive of acute or worsening chronic renal failure. Gastrointestinal AEs, including nausea, diarrhea, and vomiting, have been reported with tirzepatide. These are consistent with other GLP-1 receptor

agonists. The events may lead to dehydration, which could cause a deterioration in renal function, including acute renal failure. Patients will be advised to notify investigators in case of severe nausea, frequent vomiting, or symptoms of dehydration.

#### Severe gastrointestinal adverse events

Tirzepatide may cause severe GI AEs, such as nausea, vomiting, and diarrhea. The eCRF will collect information about any intolerance or persistent GI AEs and antiemetic/antidiarrheal use. For detailed information concerning the management of GI AEs, please **see Annex 8**.

#### Thyroid Malignancies and C-cell hyperplasia

Individuals with a personal or family history of MTC and/or MEN-2 or screening calcitonin >35ng/L will be excluded from the study. The assessment of thyroid safety during the study will include reporting any case of thyroid malignancy, including MTC and papillary carcinoma, and calcitonin measurements. This data will be captured in specific eCRFs. The purpose of calcitonin measurements is to assess the potential of tirzepatide to affect thyroid C-cell function, which may indicate the development of C-cell hyperplasia and neoplasms. Tirzepatide should be discontinued (after first confirming the value) if the post-randomization calcitonin value is  $\geq 35$  ng/L and has increased at least 50% over baseline. We will evaluate the concomitant medication for other potential causes. If the increased calcitonin value ( $\geq 35$  ng/L and increases by  $\geq 50\%$  compared with baseline) is observed in a patient who has administered a medication that is known to increase serum calcitonin, this medication should be stopped, and calcitonin levels should be measured after an appropriate washout period. If the confirmed calcitonin value is <35 ng/L, tirzepatide should be restarted when safe (assessed by the study PI).

#### Hypersensitivity Events

The investigator will report all allergic or hypersensitivity reactions as either AEs or SAEs if any serious criterion is met. Additional data, such as the type of reaction and treatment received, will be collected on any AEs or SAEs that the investigator deems related to the study drug via an eCRF created for this purpose. The study drug should be temporarily interrupted in any individual suspected of having a severe allergic reaction to the study drug. At the investigator's discretion, the study drug may be restarted when/if deemed safe. If the study drug is permanently discontinued, the patient will continue in the trial to collect all planned efficacy and safety measurements.

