#### **7.4 Criteria for withdrawal/discontinuation of participants**

Participation in this research is voluntary. Participants may withdraw at will at any time. When withdrawing from the study, the participant should let the research team know that he/she wishes to withdraw. The participant is not required to provide a reason.

The investigator must stop the study intervention for the individual participant if any of the following criteria are met:

- Withdrawal of informed consent
- Confirmed pregnancy.
- Actively trying to become pregnant.
- Developing an allergic reaction to tirzepatide.
- If the inclusion and exclusion criteria are no longer met.
- Non-compliance with the study procedures, or
- At the investigators' judgment due to safety concerns (**See Subsection 9.4.1** for the definition of adverse events and other safety-related events).

After withdrawal, the participant will be given instructions on how to safely stop using the IMP and, eventually, on how to return to the previous treatment regimen correctly and safely. Instructions are also given on who to contact if any questions or concerns arise after study withdrawal. Any data collected until study withdrawal will remain coded for the analysis.

Withdrawn participants will not be replaced. However, at the investigator's discretion, re-screening is allowed within the recruitment period to complete 42 participants. Further information about the follow-up procedures is available in **Subsection 9.2.5**.

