## 9.2.5 Assessments in participants who prematurely stop the study.

### Individual participant-stopping criteria.

Study drug administration may be stopped for any of the following reasons:

- Three or more episodes (separated by at least 120 minutes) of clinically significant hypoglycemia (Level 2) within one day (defined as 00:00 – 23:59) of the study, after excluding other causes such as the omission of meals, unexpected increases in physical activity, or exercise (or any other contributing factor more likely than the IMP) (**See Annex 10**).
- One or more episodes of severe hypoglycemia (Level 3) (**See Annex 10**).
- One or more DKA events unrelated to the participant's AID system malfunction.
- Adjudicated hepatic or pancreatic AEs.
- Incidence of allergic and hypersensitivity reactions.
- If a participant misses three or more consecutive doses of tirzepatide due to intolerable GI symptoms (e.g., nausea, vomiting, or diarrhea) that could be reasonably attributed to the study drug, despite the mitigation plan (**See Annex 8**).
- If a participant is diagnosed with an active or untreated malignancy (other than basal or squamous cell skin cancer, in situ carcinomas of the cervix, in situ, or grade group 1 [that is, Gleason 6 or lower] prostate cancer) after randomization.
- Dehydration or renal acute events.
- Post randomization calcitonin value  $\geq 35$  ng/L and increased at least 50% over baseline.
- Supraventricular arrhythmias and cardiac conduction disorders.
- If a female participant becomes pregnant.
- Investigator decides that, in the interest of the patient, it is not medically acceptable to continue participation in the study.
- Participants with a normal BMI at baseline will be closely monitored during clinical visits. The medication will be reduced to 2.5 mg or discontinued if there is a weight gain that exceeds 5% of total body weight or if weight reduction is too rapid (defined as greater than 1% of total body weight per week) following clinical evaluation

**Table 1** describes the time points of assessment. For the definition of these AEs/SAEs and for follow-up and procedures for participants who prematurely stop the study, see **Subsection 10.1.2**.

Criteria for suspending or stopping the study.

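### Section 7.4 requires tirzepatide to be stopped for any allergic reaction to it, but sections 9.2.5 and 10.1.2 leave the stop and the restart to discretion without reference to that rule

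*Protocol*

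**What the plan says.** Three parts of the protocol tell the site what to do with the drug when an allergic reaction occurs.

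- **Section 7.4** (withdrawal and discontinuation) is mandatory: "The investigator must stop the study intervention for the individual participant if any of the following criteria are met". One of the criteria listed is "Developing an allergic reaction to tirzepatide". It sets no severity threshold and makes no provision for restart.
- **Section 9.2.5** (individual stopping criteria) is permissive: "Study drug administration may be stopped for any of the following reasons". One of the reasons listed is "Incidence of allergic and hypersensitivity reactions".
- **Section 10.1.2, Hypersensitivity Events**, addresses the suspected severe case: "The study drug should be temporarily interrupted in any individual suspected of having a severe allergic reaction to the study drug". The next step is "At the investigator's discretion, the study drug may be restarted when/if deemed safe". It then adds that patients who stop permanently remain in the trial for the planned measurements.

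Related text stands in three other places. Section 3.7 f says that the medication is discontinued when such a reaction is suspected, without saying whether for good. Section 10.1.1, Assessment of Causality, has both the investigator and the sponsor-investigator judge the relation of each event to the drug. Exclusion criterion 10 in section 7.1.2 bars people with a history of allergy to the drug class or its excipients.

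**The concern.** One event, an allergic reaction to tirzepatide, is met by an obligation in one section, an option in a second, and in a third by interruption followed by a discretionary restart. The section with the loosest condition is the one written for suspected severe reactions, and it is where a physician handling such a case would naturally look.

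What is at stake is continued exposure or re-exposure of a participant whom section 7.4 says must come off the drug. Rules for stopping and restarting treatment belong in the protocol, not in a statistical analysis plan, so this is not detail properly left for later. The trial has no data safety monitoring committee, so at the moment of decision the site has only the protocol text to go by.

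**Working it through.** No arithmetic applies. The check sets the rules side by side and asks whether any text links them.

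| Protocol section | Trigger | Action | Condition for restart | Refers to 7.4? |
|---|---|---|---|---|
| 7.4 | Allergic reaction to tirzepatide, any severity | Must stop | None offered | – |
| 9.2.5 | Allergic or hypersensitivity reaction, cause not specified | May stop | Not addressed | No |
| 10.1.2, Hypersensitivity Events | Suspected severe allergic reaction to the drug | Interrupt; may restart | Judged safe by the investigator | No |

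Of the three, one is mandatory. Of the other two, neither refers to section 7.4.

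**Step 1: do the triggers overlap?** Yes. The entry in 9.2.5 is not limited by cause, so it includes reactions to tirzepatide. A suspected severe reaction under 10.1.2 may turn out to be an allergic reaction to tirzepatide, which is the 7.4 trigger.

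**Step 2: is there a consistent reading?** Yes. Interrupt on suspicion, assess the cause, stop for good if the reaction was an allergic one to tirzepatide, and otherwise consider restarting. Under this reading 7.4 prevails and the other two sections fill in around it.

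**Step 3: does the protocol state that reading?** No. The restart sentence in 10.1.2 depends only on a judgement of safety. It does not ask whether tirzepatide was the cause, and it does not say that it is subject to 7.4. Section 9.2.5 likewise does not reserve reactions to tirzepatide for the mandatory rule.

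**Step 4: do the cross-references supply the link?** No. Section 7.4 sends the reader to 9.2.5 ("Further information about the follow-up procedures is available in" that subsection), and 9.2.5 sends the reader on to 10.1.2 for definitions and follow-up. Nothing in 9.2.5 or in the hypersensitivity text leads back to 7.4.

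**Step 5: does the causality assessment supply the link?** Not as written. Section 10.1.1 requires the assessment, and section 9.2.4 has the relation to treatment recorded for every adverse event. But no passage makes its result a condition of restarting.

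**Step 6: how is a restart written elsewhere in the same section?** The calcitonin rule, shortly before the hypersensitivity text, has the participant restart when it is safe, but only once a confirmed value is below 35 ng/L. A stated finding comes first and the safety judgement second. The hypersensitivity text has only the second.

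**The case against.** The strongest reply is that there is no true contradiction. Section 7.4 covers an allergic reaction that has developed, while 10.1.2 covers suspicion and names interruption as the first action. An obligation binds once its trigger is met, and a permissive list elsewhere does not repeal it. The list in 9.2.5 covers reactions of any cause and mixes in matters of clinical judgement. It also includes "If a female participant becomes pregnant", where other sections plainly require a stop and nobody would think the stop optional. Causality is assessed for every event, and exclusion criterion 10, together with the 7.4 clause on eligibility criteria no longer being met, arguably provides a second mandatory stop. The pointers between sections concern follow-up, not the stopping rule. The calcitonin comparison is imperfect, because an allergic reaction has no numerical re-test.

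Much of this stands, and it rules out stronger readings that a reader might infer:

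- **That the protocol authorises re-exposure after an established allergy to tirzepatide.** It does not; the restart text is about suspicion.
- **That 9.2.5 cancels 7.4.** It does not; it only fails to repeat or cite it.
- **That nobody has to judge the cause.** Sections 10.1.1 and 9.2.4 require it.
- **That section 3.7 f is a further conflict.** Discontinuing on suspicion is compatible with 10.1.2 as a first action, since 3.7 f does not say that it is permanent.

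What the reply does not remove is that the reader must supply the order of the rules. Nothing makes the causality assessment decide the restart. For a suspected severe reaction, that order should be on the page.

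**Conclusion.** The point holds as an inconsistency in operative safety text that should be fixed. One mandatory rule stands beside two discretionary ones, and neither of those is tied to it or to the causality assessment. Following 9.2.5 or the hypersensitivity text in 10.1.2 literally could breach 7.4 and leave a participant on tirzepatide, or return one to it, after an allergic reaction to it.

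The effect is on participant safety only. The protocol gives no event rate for allergic reactions; section 3.7 f describes immune and hypersensitivity reactions as generally infrequent and mostly mild to moderate, so few participants are likely to be affected. There is no effect on power, type I error or the primary analysis. A reader might also infer that the safety outcome on early discontinuation due to adverse events becomes ambiguous. The documents do not support that: the outcome concerns actual discontinuations, whichever clause led to them.

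The conclusion assumes that the mandatory rule in 7.4 expresses the sponsor's intent. Exclusion criterion 10 supports this.

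**What to change.** 1. **Section 10.1.2, Hypersensitivity Events.** State that tirzepatide is interrupted on suspicion and may be restarted only if the causality assessment in section 10.1.1 has ruled out an allergic reaction to tirzepatide; otherwise it is stopped permanently under section 7.4.
2. **Section 9.2.5.** State that an allergic reaction to tirzepatide must lead to a stop under section 7.4, and keep the optional wording only for reactions due to other causes.

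The sponsor's medical lead should settle the clinical content, including which causality category counts as ruled out. The existing scale defines its lowest category, not related, in those terms.

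Optional tidying: replace the instruction in section 3.7 f with a cross-reference, and bring acute pancreatitis and pregnancy in the 9.2.5 list into line with the mandatory stops already stated elsewhere. Those rules are not in doubt.

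The cost is a wording amendment in two places and a memo to the site, with no new visits, procedures or participants.

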#### Injection Site Reactions

Injection site reactions will be collected on the eCRF separate from the hypersensitivity reaction eCRF.

#### Supraventricular Arrhythmias and Cardiac Conduction Disorders

Treatment-emergent cardiac conduction disorders will be further evaluated. Additional diagnostic tests to determine the exact diagnosis will be performed as needed. The specific diagnosis will be recorded as an AE. Events that meet the criteria for serious conditions, as described in **Section 10.1.1**, will be reported as SAEs.

##### **10.1.2.1 Foreseeable adverse events**

Hypoglycemia or hyperglycemia events not meeting the above criteria are not required to be reported as an adverse event.

Participant's own devices (e.g. insulin pump, CGM, BG meters) related issues and skin issues arising from using these devices (such as skin rash due to adhesive or infusion site issues) are not reportable unless the event meets the definition of an SAE.

##### **10.1.2.2 Reporting of SAEs**

All SAEs will be reported to the study Sponsor immediately and within a maximum of 24 hours. The Sponsor-Investigator will re-evaluate the SAE in REDCap. SAEs resulting in death will be reported to the Ethics Committee via BASEC within seven days.

##### **10.1.2.3 Reporting of SUSARs**

A SUSAR needs will be reported to the Ethics Committee (local event via local Investigator) via BASEC and Swissmedic via the Sponsor-Investigator within seven days if the event is fatal or within 15 days (all other events).

##### **10.1.2.4 Reporting of immediate safety and protective measures**

All suspected new risks and relevant new aspects of known adverse reactions that require immediate safety-related measures will be reported to the Sponsor-Investigator within 24 hours. The Sponsor/Investigator will report these measures within seven days to the Ethics Committee (local event

via local Investigator) via BASEC and Swissmedic.

#### **10.1.2.5. Reporting and Handling of Pregnancies**

Pregnant participants will be immediately withdrawn from the clinical study. Any pregnancy during the treatment phase of the study and within 30 days after discontinuation of study medication will be reported to the Sponsor/Investigator within 24 hours. The course and outcome of the pregnancy will be followed up carefully, and any abnormal outcome regarding the mother or the child will be documented and reported.

#### **10.1.2.6 Periodic reporting of safety**

The ASR is written in compliance with ICH Harmonised Guideline E2F for a non-commercial sponsor.

An ASR is submitted once a year to the Ethics Committee and to Swissmedic via the Sponsor-Investigator.

The start date for the ASR is the date of the sponsor's first authorization to conduct a clinical trial

The ASR is submitted to the Ethics Committee and Swissmedic throughout the clinical study in Switzerland, and the last ASR submission will cover the last patient-last visit.

#### **10.1.3 Follow-up of (Serious) Adverse Events**

Follow-up of adverse events: The investigator will provide adequate medical care to the study participants for any study-related adverse events, including clinically significant laboratory values related to the study. Medical care should be provided to the participants regardless of their insurance status. AE classified as serious or possibly/probably related to the study drug will be followed until the participant has recovered and all queries have been resolved or until the end of the post-treatment follow-up stated in the protocol, whichever comes first.

The medical assessment, vital signs, and laboratory measurements are documented and reported as applicable to the specific event. Participants will be called in case otherwise cannot be reached.

#### **10.2 Assessment, notification, and reporting on the use of radiation sources**

Not applicable

## 11. STATISTICAL METHODS

### 11.1 Hypothesis

The primary outcome of this study is the Mean difference in 24/7 CGM percentage time spent between 3.9 and 10 mmol/L (TIR) between groups at week 16 of treatment (**Figure 1**). The difference in TIR will be established in a parallel design using a statistical significance of  $\alpha=0.05$ .

The null/alternative hypotheses are:

- Null hypothesis: There is no mean 24/7 CGM-based TIR difference between tirzepatide+AID (intervention) vs. SoC+AID (control) at 16 weeks of treatment.
- Alternative hypothesis: The mean for 24/7 CGM-based TIR differs for tirzepatide+AID (intervention) and SoC+AID (control) at 16 weeks of treatment.

### 11.2 Determination of Sample Size

Assuming a 1:1 randomization ratio, we calculated that a sample size of 42 participants (21 in each arm) would provide 80% power with a type I error rate (two-sided) of 5% to reject the null hypothesis with the following assumption: a standard deviation (SD) at baseline for TIR of 15%, a pre-post difference of TIR in the control group of 0.2%, a pre-post difference of TIR in the treatment group of 10.5%, a correlation of 0.7, and an attrition rate of 20%. The assumptions were taken from retrospective studies in T1D using tirzepatide (34,35).

### 11.3 Statistical criteria for termination of trial

As described in **Subsection 9.2.5**.

### 11.4 Planned Analyses

This study will assess the safety and efficacy of tirzepatide (*Mounjaro*®) added to existing AID systems through a change in TIR and secondary and exploratory endpoints, including other CGM-based metrics, HbA1c, and surrogate endpoints for CVD, MAFLD, and renal markers. All variables will be tested for normality with the Shapiro-Wilk and/or the Kolmogorov-Smirnov tests. Continuous and normally distributed data will be presented as mean $\pm$ SD and categorical as N%. Non-normally distributed variables will be analyzed using non-parametric tests and presented as median [IQR]. Stata software version 18 and IBM SPSS statistics version 30.0.0 will be used for the statistical analyses.

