#### 11.4.2 Primary Analysis

The study design allows repeated measures (before and after) of the primary outcome and exploratory outcomes. We will use repeated measures analysis of covariance (ANCOVA) for the primary outcome while adjusting for HbA1c, BMI, and baseline TIR. A point estimate 95% confidence interval and two-sided p-value will be reported for the interventions (tirzepatide+AID vs SoC+AID), and a 5% level will be used to declare statistical significance. Residual values will be examined for an approximate normal distribution.

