#### **11.4.5 Safety analysis**

The entire ITT population will be included for safety analysis (such as AE/SAE). A table will be populated with the frequency of system-wide adverse events between two groups. Differences in safety outcomes will be examined between ITT groups using Chi-Square tests for categorical outcomes (any AE/SAE, clinically significance hypoglycemia, severe hypoglycemia, DKA) and non-parametric tests for continuous variables with non-normal distribution such as time spent in hypoglycemia on CGM.

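### A normality pre-test that sends non-normal variables to an unnamed non-parametric test contradicts the ANCOVA and MMRM fixed for the same endpoints, and no rule says which prevails

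*Protocol*

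**What the plan says.** Section 11.4 (Planned Analyses) opens with a general rule: "All variables will be tested for normality with the Shapiro-Wilk and/or the Kolmogorov-Smirnov tests". The consequence follows: "Non-normally distributed variables will be analyzed using non-parametric tests and presented as median [IQR"]. The rule exempts no endpoint, does not name the replacement test, and does not say which normality test decides if the two disagree.

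Section 11.4.2 prescribes an ANCOVA for the primary outcome, adjusted for HbA1c, BMI and baseline TIR, reported as an estimate with 95% confidence interval and p-value. Its own check concerns the model: "Residual values will be examined for an approximate normal distribution". It states no consequence of that check. Section 11.4.3 prescribes an MMRM for the secondary outcomes, with the same reporting and the same residual check.

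Section 11.4.5 (Safety analysis) plans "non-parametric tests for continuous variables with non-normal distribution such as time spent in hypoglycemia on CGM". Percent time below 3.9 and below 3.0 mmol/L are also hierarchically tested secondary outcomes: sixth and eighth in the synopsis list, sixth and seventh in the Section 5 list.

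**The concern.** Sections 11.4 and 11.4.2–11.4.3 give different instructions for the same endpoints. Section 11.4 tests the variables themselves and lets the result choose the analysis. The later sections fix the analysis and look at residuals, which is where the normality assumption of these models lies.

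Three things are at stake.

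- **Pre-specification.** An analyst who follows Section 11.4 as written chooses the confirmatory test after seeing the data, in an open-label trial, with an open choice of normality test and an unnamed replacement.
- **The question answered.** The hypotheses in Section 11.1 and the outcomes in Section 5 are differences in means. A two-sample rank test reported with medians addresses something else and gives no adjusted mean difference.
- **The hierarchy.** Percent time below 3.9 mmol/L is sixth in both lists, so its test decides whether the later endpoints may be tested. With two analyses described for that measure, the one that opens or closes the gate should be known in advance.

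**Working it through.** **Inputs (Section 11.2).** The plan states "a sample size of 42 participants (21 in each arm") that "would provide 80% power with a type I error rate (two-sided) of 5% to reject the null hypothesis". It assumes "a standard deviation (SD) at baseline for TIR of 15"%, changes of 0.2 points (control) and 10.5 points (treatment), a correlation of 0.7 and 20% attrition. The difference is 10.5 − 0.2 = 10.3 points. The synopsis says that the calculation is based on an ANCOVA.

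**Step 1: reproduce the stated size.** Per-arm n = 2 × (1.960 + 0.842)² × SD² / 10.3², rounded up.

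| Analysis | SD | n per arm | Total after attrition (2n / 0.8, rounded up) |
|---|---|---|---|
| ANCOVA | 15 × √(1 − 0.7²) = 10.71 | 17 | 34 / 0.8 = 42.5 → 43 |
| Change score | 15 × √(2 × (1 − 0.7)) = 11.62 | 20 | 40 / 0.8 = 50 |
| Week-16 value, unadjusted | 15 | 34 | 68 / 0.8 = 85 |

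Multiplying 17 by 1.2 gives 20.4, hence 21 per arm and exactly 42. Only the ANCOVA variance comes within two participants of the stated 42, so the planned power depends on baseline adjustment of TIR.

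**Step 2: power if the switch happened for TIR.** There were 20,000 simulated trials with normal data and the planning values. ANCOVA was adjusted for baseline TIR only. The Mann-Whitney test stands in for the unnamed test.

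| Analysis | 17 per arm | 21 per arm |
|---|---|---|
| ANCOVA | 76.5% | 85.4% |
| Mann-Whitney on change | 68.2% | 77.5% |
| Mann-Whitney on week-16 value | 47.4% | 55.8% |

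For ANCOVA at 17 per arm, a non-central t calculation gives 77.5% and the normal approximation 80.0%. Because the simulated data are normal, the loss comes from the change of test and not from a violated assumption.

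**Step 3: how often the switch would be triggered.** This is Shapiro-Wilk at the 5% level on 34 pooled values, 5,000 runs each. The protocol gives no distributions and no significance level for the normality test, so these are assumptions.

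| Assumed distribution | Rejected |
|---|---|
| TIR normal | 4.3% (nominal 5%) |
| TIR beta, mean 65%, SD 15% | 11.5% |
| Time below range beta, mean 2%, SD 2% | 98.3% |

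**Step 4: average loss for the primary.** This is trigger probability times loss, treating pre-test and test as independent and carrying over the loss from normal data.

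- Mann-Whitney on change, loss 76.5 − 68.2 = 8.3 points: 5% × 8.3 ≈ 0.4; 11% × 8.3 ≈ 0.9.
- Mann-Whitney on week-16 values, loss 76.5 − 47.4 = 29.1 points: 5% × 29.1 ≈ 1.5; 11% × 29.1 ≈ 3.2.

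The range is roughly 0.4 to 3 points.

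**Step 5: the hypoglycaemia measures.** Section 11.4.3 covers all secondary outcomes, so percent time below 3.9 and below 3.0 mmol/L go to the MMRM. Section 11.4 would move them to a non-parametric test if the pre-test rejects, and Section 11.4.5 uses time in hypoglycaemia as its example of such a variable. None of the three says which result feeds the hierarchical sequence.

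**The case against.** The best defence is that Section 11.4 is a general lead-in on presentation and software, while 11.4.2 and 11.4.3 are specific to the endpoints and unconditional. Reading the specific over the general leaves the primary test fixed. That is a sensible reading, and it is why this is an unresolved contradiction: a reader might infer that Section 11.4 overrides the ANCOVA, but the protocol states no order of precedence in either direction. The defence does not remove the problem, because Section 11.4 speaks of how variables are analysed as well as how they are presented, and its opening sentence mentions TIR, other CGM metrics and HbA1c.

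A reader might also infer that primary power drops to 47%. That figure needs both the least favourable candidate test and a trigger that is unlikely for TIR. A baseline-adjusted rank method would also satisfy the wording of Section 11.4 and would lose much less.

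Nor does the planned power rest on the MMRM. The sample size concerns TIR under ANCOVA alone.

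Finally, the test in Section 11.4.5 may be meant as a separate safety comparison, which can coexist with an efficacy model. That is fair, but the analysis that governs the hierarchical test still needs to be stated.

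**Conclusion.** The point stands as a contradiction within the protocol that should be resolved before the data are seen. It is not a detail left to a statistical analysis plan, since the protocol itself states two incompatible rules.

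For the primary endpoint the practical risk is modest. If the switch were triggered, power at 17 per arm would fall from about 77% to between 47% and 68%, depending on the test. With a trigger probability of about 5% to 11%, the average loss is about 0.4 to 3 points. The larger issue there is that the confirmatory test could depend on the data.

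For time below range the conflict is likely to arise in practice, with a trigger probability of about 98% if its mean and SD are both near 2%. The documents give no distribution for this or any other skewed CGM metric, so near certainty is conditional on that assumption and was not examined for time above 13.9 mmol/L.

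**What to change.** - Delete the switching rule in Section 11.4. Keep normality tests, and medians with interquartile ranges, for description only.
- State that the ANCOVA for TIR and the pre-specified model for the secondary outcomes stand whatever a normality test shows. Any rank-based analysis becomes a named sensitivity analysis.
- For percent time below 3.9 and below 3.0 mmol/L, name in advance one baseline-adjusted analysis that governs the hierarchical test. The choice of method is the sponsor's, provided that it is fixed beforehand.
- Label the comparison of time in hypoglycaemia in Section 11.4.5 as a descriptive safety comparison outside the hierarchy.

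The cost is wording and a few lines of analysis code. Sample size, visits and data collection do not change.
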